## Abstract

The medico-legal care of victims of sexual assault is very challenging, and requires specific knowledge and skills. Professionals in the emergency departments of hospitals might not have specialised training in forensic science. Nurses have a very significant role in these settings, but they lack any formal forensic training. This study aims to develop a sexual assault nurse examiner-grounding program (SANE-GP) for Indian nurses to inculcate knowledge and skill regarding sexual assault examination. The study adopts a three-stage Delphi technique to develop the training module and uses a time-series design to evaluate the effectiveness of the program. A questionnaire on nurses’ knowledge on sexual assault examination (KQSANE-I) will be developed in phase-I and subsequently used in phase-II. The protocol of SANE-GP will help the medical community to implement the program across India. The implementation of SANE-GP can also help to start a sexual assault nurse examiner network.

## List of abbreviations

ASO: Alternative Sexual Orientation

CrPC: Criminal Procedure Code

DAC: Dissertation Advisory Committee

KQSANE-I: Questionnaire on nurse’ knowledge about sexual assault examination

POCSO: The Protection of Children from Sexual Offences Act

SAE: Sexual Assault Examination

SAFE: Sexual Assault Forensic Examination

SANE: Sexual Assault Nurse Examiner

SANE-GP: Sexual Assault Nurse Examiner-Grounding Program

WHO: World Health Organization

## Introduction

Sexual violence is a huge concern and has malignantly affected all strata of our community regardless of age, gender, race, ability, and social status. However, the estimates of incidents of sexual violence around the globe suggest that there is a predominance of sexual violence against women in comparison to the sexual violence against men. The annual report “Crime in India – 2019” by the National Crime Record Bureau (NCRB) indicated that a total of 4,05,861 cases of crime against women were registered in India during 2019, which includes 7.9% of rape cases. The crime rate registered per lakh women population was 62.4 in 2019 in comparison with 58.8 in 2018 (
National Crime Records Bureau (NCRB), 2019). Sexual violence affects many aspects of the victim’s life including personal safety, their family, interpersonal relationships, finance, and work environment, and makes the victim undergo perplexity of investigation and legal trial. Unfortunately, in some cases the medical, legal and law enforcing agencies operating in the country and the society itself, make the victim feel the sexual assault was their fault and re-victimise them for someone else’s cruelty. (
Relyea and Ullman, 2017). Most of the time, the trauma they are already undergoing, is much less than the trauma they receive from the system — a system that is supposed to help them (
Maier, 2008). Sexual offenses are under-reported to law enforcement agencies due to fear of retaliation and humiliation (
Shanmugam, 2013;
Flecha, 2021). A comparative study of the NCRB data on rape and the National Family Health Survey shows that only 0.6% of women who faced sexual violence filed a complaint to the police (
Rukmini, 2014). The legal system of India is common to all states and union territories. The judiciary is independent and not governed by the federal government. The time taken for a case to come to trial in the Indian court is getting longer. Crimes against women and an increase in the incidents of criminal activities have contributed to the workload of the judiciary system (
Jaithlia and Maheshwari, 2020).

When victims are being re-victimised by the system, most of them will not go to the hospital and report that they were sexually assaulted and are also not willing to follow the criminal justice system (
Maier, 2012). This causes a significant underestimation of the prevalence of crimes against women and children (
Murshid and Bowen, 2018;
Jennings, Powers and Perez, 2021). The Criminal Law Amendment Act 2013 widened the definition of rape and acknowledges the right to get medical and forensic attention to all victims and survivors of sexual assault by health care centres in public as well as private sectors. Failure to provide health care services is now considered an offence under this law. The right to treatment requires the state to guarantee that adequate, good quality proper medical, forensic, and mental health services are accessible to the victims without any discrimination (
Ministry of Health and Family Welfare (MOHFW), 2014). An excellent health care service requires professionals who can treat injuries, do medico-legal examinations, collect evidence, provide prophylaxis, test for sexually transmitted infections, administer emergency contraception, and give psychosocial support to the victims.

The Indian health care delivery system is constituted in such a way that most of the reported sexual assault cases are managed by the emergency departments of the hospitals that do not have health care professionals with specialised training in forensic science (
Saxena *et al.*, 2015;
Lingam *et al.*, 2021). The situation is similar in state-run as well as in private hospitals, except for certain medical colleges. The emergency team consists of doctors, nurses, and paramedics, in which doctors have the minimum qualification of Bachelor of Medicine and Bachelor of Surgery (MBBS). The curriculum of MBBS contains a para-clinical subject of ‘forensic medicine including toxicology’, which is a stand-alone exposure to the field of forensic sciences. The Indian legal system give preferences to female doctors for the examination and evidence collection from the survivors of sexual assault (
Ministry of Health and Family Welfare (MOHFW), 2014). However, the number of female doctors in the country are low (
Rao *et al.*, 2011) and female nurses are more in number and they are easily accessible to the system and well accepted by the survivors. When considering the cost of the basic health care services nurses are cost effective compare to the doctors. In any medical or health care setting nurses are the ‘first point of care’ and have very crucial role in the examination and evidence collection from the victims of sexual assault (
[name] *et al.*, 2022e). The female nurses are sensitive to their patients’ physical and emotional needs and able to develop early rapport with the victims of sexual assault, which will lead to better acceptance and allows the victim to open up during the time of history collection and medico-legal evidence collection (
Campbell *et al.*, 2013). However, nurses lack forensic training in any form, and the casual examinations can cause missing of vital evidences (
Dash *et al.*, 2016).

In developed countries, nurses have a very significant role in the field of emergency and trauma care, toxicology, crime scene investigation, and correctional settings (
Henninger *et al.*, 2020). Strengthening forensic nursing education in the country is critical as the crimes against the women and children are increasing. There is a wider scope for forensic nursing in India and the nurses can take roles in medico legal investigations and evidence collection (
Lynch, 2011;
Renjith *et al.*, 2016).

### Research gap

Medico-legal care of the victims of sexual assault is very challenging as it involves medical, legal, and ethical aspects. The curriculum of BSc Nursing, as well as General Nursing and Midwifery, does not deal with forensic clinical examination and the collection and preservation of evidence. Unlike the sexual assault referral centres (SARC) in the global scenario, India does not have such designated centres, and the victims are taken care of by the health care centres and state-run hospitals.

The nurse in the health care centres needs to be competent enough to handle the medico-legal cases that require specific knowledge and skills (
Alsaif *et al.*, 2014). Training on a wide range of issues is important for the nursing staff handling medico-legal cases (
Zerbo *et al.*, 2018). These include positioning and examination of the client, obtaining high-quality specimens, identifying and reporting genital-anal injuries after sexual assault, comparing the injuries of consensual and non-consensual intercourse, identifying and collecting traces from the fingernail and other materials for the DNA analysis of the aggressor and employing DNA evidence in sexual offence cases to aid the identification of suspects, movement of forensic evidence and chain of custody, analysing and preventing drug-facilitated crimes against women, usage of photo colposcopy to identify hymenal transections and other injuries in children and adult females, simulation, forensic photography, bite-mark identification, handling vicarious trauma and mindfulness based interventions for better coping. Peer support is also essential for nurses to be able to cope with the demands of working in such situations (
Drake and Adams, 2015;
Gharedaghi *et al.*, 2018;
[name] *et al.*, 2018, 2021;
Rodriguez *et al.*, 2019;
Usman *et al.*, 2019;
Yassa and Badea, 2019;
McAllister and Vennum, 2021;
Zweig *et al.*, 2021).

A lacuna is identified in the literature related to forensic examination of sexual assault victims. A few studies were identified which assess the knowledge of nurses and student nurses in forensic medical examination. However, no studies were reported from India or Asia regarding the knowledge and skills of nurses in forensic examination and evidence collection.

### Conceptual framework

The attribute service quality model by Haywood-Farmer was adopted as the conceptual framework for this study (
Haywood-Farmer, 1988). This model states that a service organisation is termed high quality if it consistently meets customer preferences and expectations. The separation of attributes into various groups is the first step towards developing service quality. The three types of quality attributes of health care services are physical and process components, behavioural elements, and elements of professional judgment.

### The study

The proposed research is designated to determine the level of the nurse’s competence and knowledge in the examination and management of sexual assault and investigate the effectiveness of multicomponent training in improving knowledge and skill. Implementation of multicomponent training enables nurses to communicate efficiently, examine precisely, collect and preserve evidence accurately and present it properly before the court of law.

The increase in the number of sexual crimes against women and children, stringent guidelines and protocols issued by the government, the influence of mass media, and increased social pressure demands health care professionals to be more accurate and sensitive in handling cases of sexual assault. The findings of the study will help to develop a protocol for nurses, and the same can be utilised as a model guideline for nurses in India. The findings of the study are expected to initiate the sexual assault nurse examiners network (SANE network) in the Udupi district, which can be adopted to other districts.

### Research objectives

i.Develop a valid and reliable instrument to measure the knowledge regarding SAE among nursesii.Develop a SANE-GP module using a three-stage Delphi methodiii.Explore the effectiveness of SANE-GP on the knowledge and skill regarding SAE.iv.Develop a platform for the SANE network in the country

## Protocol

### Design

The proposed study adopts a cross-sectional survey design in Phase-I and an experimental design to meet the objectives in Phase-II. The study also uses a Delphi technique for the development of a module for the SANE-GP.

*Phase-1*

Objective 1: A questionnaire on nurses’ knowledge about sexual assault examination-(KQSANE-I) will be developed based on the Robert F DeVellis method of tool development (
DeVellis, 2016), which includes item development, item pooling, content adequacy assessment, clarification of the items, refining the items, the administration of questionnaire (empirical testing after determining the scale for items and adequate sample size), item analysis, reliability assessment, and construct validity. The administration of the questionnaire will be conducted through a survey, and the data will be collected from 450 participants. Skill questionnaires and practice checklists will be developed along with the development of the SANE-GP module.

Objective 2: Delphi techniques of data collection with experts in the field of forensic science to develop a SANE-GP module for nurses.

*Phase-2*

Objective 3: The study proposes to have one group with a before and after experimental design with three follow-ups to evaluate the effectiveness of SANE-GP among nurses working in the hospital.

### Research setting and population

Phase-I of the study will be carried out amongst the registered nurses from private and state-run hospitals from Udupi and Dakshina Kannada districts of Karnataka, India. Participants will be included from both genders. A three-stage ‘Delphi’ technique will also be initiated to develop the module for Phase-II. The experts are from the field of forensic medicine and forensic nursing from the national and international arena. In the second phase, 74 nurses from a selected tertiary care hospital will be recruited for the training of SANE-GP and subsequent assessment of the effectiveness of the program.

### The sampling technique

In Phase-I, the item pool, which is developed after reviewing the current literature and validated with the experts, will be administered to 450 registered nurses who are willing to participate (see
*Extended data,*
[name] *et al*., 2022a). The sampling technique adopted is purposive sampling. For the development of the module for SANE-GP, Delphi technique data collection will be conducted in three stages. Each stage of Delphi will have seven experts from the field of forensic medicine and forensic nursing. A five-step process will be utilized for the selection of the panel members: i) review the literature and make a list of potential experts based on the recent work in sexual assault examination, ii) check citation index for number of citations, iii) evaluate each expert’ work and grade them on a scale of three, iv) present the potential experts’ work to the Dissertation Advisory Committee (DAC) and develop and final list of experts, v) contact each expert through mail or telephone and explain the purpose with an invitation to participate. A personalised email invitation will be sent to the experts agreed to participate in the study.

### Sample size

The sample size is calculated for Phase-I based on the item to response ratio of 1:10 given by
Schwab (1980). The KQSANE-I is planned to have a minimum of 44 items, hence, the sample size calculated for Phase-I is 450. For Delphi, seven experts will be recruited for participating in the study. The sample size calculated for Phase-II is based on the time series analysis using the formula n = [Z
_1-α/2_ + Z
_1-β_]
^2^ σ
^2^ [1 + (m − 1)ρ]/md
^2^ (where, n is the sample size, Z
_1-α/2_ at α = 0.05 = 1.96, Z
_1-β_ at 80% power = 0.84, σ = standard deviation (23.75), ‘m’= number of follow ups (3), ‘ρ’ = intraclass correlation (0.4), ‘d’ = clinically significant difference (7)). The sample size is calculated with an anticipatory non-response rate of 25% which is 74. The participants will be recruited through purposive sampling for SANE-GP.

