### The plan for data analysis

The researchers will use statistical software by IBM (IBM SPSS Statistics, RRID:SCR_019096),
SPSS statistics 26 (Armonk, NY: IBM Corp) for the analysis. In Phase-I, the data will be summarised using descriptive statistics and will be presented in a summary table. The knowledge score will be assessed four times (one before SANE-GP and three follow-ups), and the scores will be compared and analysed with the help of time-series analysis. The skill of the participants will be assessed after the completion of each module, and the score will be described in tables. The practice of the random participants will be assessed and described.

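### The Phase-II sample-size formula leaves out the pretest; if its SD and correlation are raw-score values that also apply at pretest, power at 55 completers is about 67–69%, not 80%

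*Protocol article*

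**What the plan says.** The Design section (Phase-2, Objective 3) describes a single-group study: "The study proposes to have one group with a before and after experimental design with three follow-ups to evaluate the effectiveness of SANE-GP". The Limitations section confirms that there is neither randomisation nor a control. The plan for data analysis sets out what is compared: "The knowledge score will be assessed four times (one before SANE-GP and three follow-ups"), with follow-ups at weeks 8, 16 and 24 according to the Data collection section.

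The Sample size section prints the formula n = (Z₁₋α/2 + Z₁₋β)² σ² [1 + (m − 1)ρ] / (m d²) and its inputs: Z "at α = 0.05 = 1.96", Z "at 80% power = 0.84", "σ = standard deviation (23.75"), "m’= number of follow ups (3"), "ρ’ = intraclass correlation (0.4"), and d = 7 as the clinically significant difference. It concludes: "The sample size is calculated with an anticipatory non-response rate of 25% which is 74".

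The section does not say whether σ and ρ describe the knowledge score itself or its change from pretest. It also does not say which contrast among the four assessments is powered.

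**The concern.** The term σ²[1 + (m − 1)ρ]/m is the variance, per participant, of the mean of m equally correlated scores. With m counting only the three follow-ups, the formula sizes a test of the follow-up mean against a constant. The study has no such constant. Its reference is the pretest mean, which is estimated from the same nurses and carries its own sampling variance and its own covariance with the follow-ups. Neither appears in the formula.

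The 80% power claim for the effectiveness question is at stake. On the plain reading of the inputs, a programme that delivers exactly the 7-point difference would be missed about one time in three rather than one time in five, once the planned 25% loss has occurred.

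**Working it through.** **Inputs (all from the Sample size section).** Z values 1.96 and 0.84; σ = 23.75, so σ² = 564.0625; m = 3; ρ = 0.4; d = 7; non-response 25%.

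**1. The plan's own figure.**
n = (1.96 + 0.84)² × 564.0625 × [1 + 2 × 0.4] / (3 × 49) = 7.84 × 564.0625 × 1.8 / 147 = 54.15, rounded up to 55.
55 / 0.75 = 73.3, rounded up to 74. The stated number is reproduced.
The variance factor in use is 1.8 / 3 = 0.60. With it, 55 completers give 80.6% power (normal) or 79.1% (t).

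**2. The same inputs with the pretest included.** Take the contrast as the mean of the three follow-ups minus the pretest, with equal SDs and one correlation ρ between all four scores. The variance per nurse is
σ² { [1 + (m − 1)ρ]/m + 1 − 2ρ } = σ² (1 − ρ)(1 + 1/m).
Factor: 0.60 + 1 − 0.80 = 0.80.

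- Completers needed: 7.84 × 564.0625 × 0.80 / 49 = 72.2, so 73. At 25% loss, 73 / 0.75 = 97.3, so 98 recruited.
- Power at 55, normal: Φ(7√55 / (23.75√0.80) − 1.96) = 68.6%. Paired t with 54 df: 67.0%. A simulation of 100,000 trials also gave 67.0%.
- Detectable difference at 55 with 80% power: 2.8 × 23.75 × √(0.80/55) = 8.02 points.
- Power if all 74 complete: 80.9% (normal) or 79.9% (t).
- One single follow-up against pretest, factor 2(1 − ρ) = 1.2: 51% (normal) or 50% (t) at 55.

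**3. Sensitivity to what the plan does not state.** Power at 55 completers, normal approximation, with the correlation among follow-ups held at 0.4. With k the pretest SD as a multiple of σ and r the pretest–follow-up correlation, the factor is 0.60 + k² − 2kr.

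| Pretest SD / follow-up SD (k) | Pretest–follow-up correlation (r) | Factor | Power |
|---|---|---|---|
| 1 | 0.3 | 1.00 | 59% |
| 1 | 0.4 | 0.80 | 69% |
| 1 | 0.5 | 0.60 | 81% |
| 0.9 | 0.4 | 0.69 | 75% |
| 0.8 | 0.4 | 0.60 | 81% |

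**4. The change-score reading.** If σ and ρ are the SD of, and the correlation between, changes from pretest, the printed formula is the right one for the mean of three changes and gives about 80% at 55. Such values can arise. With k = 0.8 and all raw correlations 0.4, each change has variance σ²(1 + 0.64 − 0.64) = σ², and two changes have covariance σ²(0.40 − 0.32 − 0.32 + 0.64) = 0.40σ², so their correlation is exactly 0.4.

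**The case against.** The strongest reply is that the protocol never calls σ a raw-score SD and never says that the pretest has the same SD as the follow-ups. It gives no scale, source or time point for 23.75. In a one-group study d is naturally a change, and if σ and ρ are also change-score values the formula is correct. It can be answered that, with equal SDs and a common correlation, changes always correlate 0.5, so 0.4 would not fit. That answer depends on equal SDs: step 4 of the working shows that a somewhat smaller pretest SD yields exactly 0.4. The change-score reading is therefore possible. It remains unstated, and a bare standard deviation and intraclass correlation read more naturally as properties of the score.

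A reader might draw three stronger conclusions, and the documents support none of them.
- That power simply is 67–69%. This holds only for raw-score inputs that also apply to the pretest; the table shows how far it moves otherwise.
- That the formula moves the wrong way with ρ, because it asks for more nurses as correlation rises. This is true for raw scores. For change scores, n should rise with ρ.
- That the number was miscalculated. The calculation is correct for the formula used. What is in question is whether the formula fits the design.

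It also stands that the mean of the three follow-ups minus pretest is an inferred contrast. The analysis plan refers only to a time-series analysis, and another model could have different power. The figure of 55 assumes that non-responders contribute no data.

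**Conclusion.** The point holds in conditional form. The printed formula has no pretest term, while the design compares follow-ups with a measured pretest in the same nurses and has no control. On the plain reading, with the one SD and one correlation given applied to all four assessments, the variance factor is 0.80 instead of 0.60. Power for 7 points at 55 completers is then about 67–69%, and 80% power needs 73 completers. If all 74 nurses complete, power is about 80%, so the allowance for 25% loss is in effect used up.

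The formula is right as printed only if σ and ρ describe changes from pretest. On raw-score values, about 80% at 55 completers would need a further assumption, such as a pretest correlation of 0.5 or a pretest SD of 0.8σ. The protocol states neither the one nor the other, so its 80% does not follow from its own inputs and design.

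**What to change.** 1. State whether σ = 23.75 and ρ = 0.4 refer to the knowledge score or to its change from pretest.
2. Name the powered contrast, for example the mean of weeks 8, 16 and 24 minus the pretest.
3. If they are change-score values, say so; the formula and the 74 can then stand.
4. If they are raw-score values, replace the formula with n = (Z₁₋α/2 + Z₁₋β)² σ² (1 − ρ)(1 + 1/m) / d², keep 74, and restate its properties: about 67–69% power for d = 7 with 55 completers, or 80% for d of about 8.0; about 80% for d = 7 only if all 74 complete. Show the range for other pretest correlations and SDs.

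The cost is a rewritten sample-size paragraph and, under item 4, a less favourable stated power. No participants are added. Holding 80% power for 7 points after 25% loss would instead take 98 recruited, on the same assumptions. The Study status section reports that recruitment is under way for Phase I, so the Phase-II text can still be corrected.
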